### Trial design (8)

The M^2^HepPrEP trial is an open-label, multi-site, multi-center, randomized, controlled, superiority trial with two parallel treatment arms. The study is a type-1 hybrid effectiveness-implementation study [35, 36]. PrEP eligible participants (+/− eligible for HCV treatment) will be randomized to on-site integrated care with adherence counseling (on-site arm) or off-site referral to PrEP and HCV treatment (if HCV positive) with patient navigation (off-site arm) in a 1:1 ratio using a permuted-block randomization scheme.

A sample of up to 100 trial participants and venue staff will be invited to participate in the qualitative study component. Cost-effectiveness analysis will be performed using data collected in the trial. A computer simulation model will be used to estimate the individual benefits of HCV treatment and the public health benefits of reduced onward transmission of HIV and HCV due to PrEP and HCV treatment.

The study protocol (version 1.0) follows the Standard Protocol Items: Recommendations for Interventional Trials (SPIRIT) Statement (see Fig. 1 and Additional file 1).

**Table 1 Tab1:** Sites

Sites	Miami		Montréal	
	Golden Glades Treatment Center	IDEA	Programme Relais du CIUSSS Centre-Sud-de-l’Île-de-Montréal	Cactus Montréal
Type	OAT clinic	SSP	OAT low threshold clinic	SSP
Funding	Private Insurance, Medicaid and Self-Pay	Private donations	Public	Public
Physicians on site	Yes	Weekly	On week day	No
Specialized in addiction	Yes	Yes	Yes	Yes
Number of physicians	2	2	5	0
Number of nurses	7	1	3	0,1
Other resources onsite	Counselling, drug testing, HIV prevention	OAT, wound care, HIV care	Standard and alternative OAT, primary care, provincial medical care card dispensing services, others	STI and hepatitis prevention education, telemedicine OAT clinics, HCV testing, sex worker/transgender person support
Clients per year	250	500–700	200–300	500–700

**Fig. 1 Fig1:**
[figure not shown]
**A** Participant screening timeline. **B** Participant study timeline

## Methods: participants, interventions, and outcomes

### Study setting (9)

The study is conducted in Miami, FL, USA, and Montreal, Québec, Canada. In each city, participants are recruited through their affiliation with SSP and/or OAT clinics. OAT is a relatively high-resourced setting with medical monitoring of treatment. SSP, on the other hand, are frequently low resourced, particularly in the southern USA. This environment is rapidly evolving in the context of COVID-19, however, with increased availability of more flexible and low-threshold OAT programs in the US and Canada, including integrating OAT at SSP [37–39] (Table 1).

### Eligibility criteria (10)

Individuals must meet the following criteria to be eligible to participate in the RCT: (1) being 18–64 years of age; (2) report injection drug use in the past 6 months; (3) be HIV negative; (4) provide informed consent; (5) complete a medical release form; (6) report living in the vicinity and being able to return for follow-up over 18 months; (7) be willing to use a medically acceptable form of contraception throughout the study duration (for females of childbearing potential); (8) be able to communicate in English, French, or Spanish (site dependent); and (9) be receiving services at an OAT clinic or SSP.

Individuals are excluded from study if they (1) have any disabling medical conditions as assessed by medical history, physical exam, vital signs, and/or laboratory assessments that, in the opinion of the study physician, preclude safe participation in the study or ability to provide fully informed consent; (2) have any disabling mental conditions as assessed by medical history and clinical assessment that, in the opinion of the study physician, precludes safe participation in the study or ability to provide fully informed consent; (3) have chronic renal failure; (4) have or have history of decompensated cirrhosis; (5) diagnosed with HIV or have symptoms of an acute HIV infection; (6) are pregnant (verified via pregnancy test), are planning to become pregnant during the course of the study, or breastfeeding; (7) have an allergy or contraindication to one of the study medications; (8) have prior HCV treatment failure with direct-acting antiviral (DAA) regimens (except in case of demonstration in medical record of SVR12 followed by reinfection); (9) are currently on PrEP and/or receiving HCV treatment; and (10) are currently in prison or jail, in any inpatient overnight facility as required by court of law or have a pending legal action, which may prevent an individual from completing the study.

### Who will take informed consent? (26a) Additional file 3

Participants are invited to participate in the study either by the service or the study staff while they are receiving services either at the SSP or OAT sites. Both screening and trial informed consent forms are distributed to participants and explained by study interviewers and/or research nurses. Participants are offered time to read, understand, and ask questions regarding the study and the informed consent forms.

### Additional consent provisions for collection and use of participant data and biological specimens (26b)

Whereas no additional studies are planned on this data at this time, any emergent issues affecting the protocol and/or the populations may result in additional studies.

## Interventions

### Explanation for the choice of comparators (6b)

PWID face numerous challenges while trying to navigate the healthcare system and thus PrEP and HCV treatment initiation remains low in this historically disadvantaged population. Patient navigation, either by professionals or peers, has been studied across various health conditions. Navigation has the advantage of being feasible with limited resources and without a complete reorganization of services. Despite its popularity, formal evaluation of this strategy in PrEP and HCV contexts is relatively limited. Studies to date have shown that patient navigation is associated with a modest, but not always significant, improvement in treatment uptake, such as a higher rate of initiation or shorter delays in initiation [40–43]. Navigation helps individuals facing some structural barriers in the healthcare system but is still limited by the need for often marginalized individuals to access care in new settings outside of their regular health or community resources [44, 45]. An alternative strategy to improve access to care is implementation of integrated, on-site services within existing OAT or SSP. However, questions remain about the relative effectiveness and the amount of resources required to provide integrated services on site.

### Intervention description (11a)

#### Pre-screening

Individuals who express interest in participating in the study meet with the study staff and are invited to provide verbal informed consent to complete a brief pre-screening interview which determines their eligibility to move forward to study screening activities. The pre-screening interview is brief and consists of questions about the individual’s sex, race/ethnicity, age, history of injection drug use, and HIV status. Individuals who pre-screen as ineligible do not continue in the study and proceed as they normally would for routine services or treatment.

#### Screening

Individuals who pre-screen as eligible and are interested in participating in the study are asked to provide written consent for the screening process and to complete a consent quiz to demonstrate their understanding of the eligibility requirements. Potential participants provide capillary blood and urine samples to complete a point-of-care HIV test, an HCV test, and a pregnancy test (for persons of childbearing potential). Venipuncture and urine samples are collected for lab tests that will further assess HIV status, HCV status, and test hepatitis B virus (HBV) status, liver function, and kidney function (Table 2). Participants complete 5 questionnaires to assess eligibility (Table 3). Participants are then contacted up to 4 weeks after their visit when their lab test results are available to complete the screening process.

**Table 2 Tab2:** Schedule of safety and clinical assessments

Assessment name	Pre-SCR	SCR	BSL	8 w	12 w	3M	16 w	20 w	6M	9M	12M	15M	18M	As clinically prescribed
Point-of-care HIV, HCV, and pregnancy rapid testing		**X**												**X**
Hepatitis A virus test, anti-HBs, anti-HBc		**X**												**X**
Pregnancy and birth control assessment		**X**	**X**			**X**			**X**	**X**	**X**	**X**	**X**	
Medical and psychiatric history		**X**												
Physical exams and vital signs		**X**												**X**
HCV Ab, HCV RNA		**X**	**X**			**X**			**X**	**X**	**X**	**X**	**X**	**X**
Liver and kidney function		**X**	**X**											**X**
HIV, syphilis, chlamydia, gonorrhea, and hepatitis B			**X**			**X**			**X**	**X**	**X**	**X**	**X**	
Concomitant medications			**X**			**X**			**X**	**X**	**X**	**X**	**X**	
Adverse events and serious adverse events			**X**			**X**			**X**	**X**	**X**	**X**	**X**	
Treatment														
Clinical management			**X**											**X**
Dried blood spot			**X**	**X**	**X**		**X**	**X**	**X**	**X**	**X**	**X**	**X**	
HCV treated participants														
HCV RNA	**12w post-Tx initiation, 12w post-end of treatment**													

*SCR* screening, *BSL* baseline, *Tx* treatment, *w* week, *M* month

**Table 3 Tab3:** Schedule of study procedures and assessments

Assessment name	Pre-SCR	SCR	BSL	3M	6M	9M	12M	15M	18M
Verbal consent and pre-screening questionnaire	**X**								
Screening informed consent form		**X**							
Locator form		**X**	**X**	**X**	**X**	**X**	**X**	**X**	**X**
Medical release authorization forms		**X**							
Injection drug use and eligibility questionnaire		**X**							
HIV and HCV testing history and readiness, knowledge		**X**							
Demographic questionnaire, health literacy		**X**							
Trial informed consent form			**X**						
Full sociodemographic survey			**X**	**X**	**X**	**X**	**X**	**X**	**X**
Substance use profile			**X**	**X**	**X**	**X**	**X**	**X**	**X**
Alcohol use, drug use			**X**		**X**		**X**		**X**
Injection profile, needle access, sharing needles and works			**X**	**X**	**X**	**X**	**X**	**X**	**X**
Overdose history survey			**X**		**X**		**X**		**X**
Attitudes towards HIV, attitudes towards HCV			**X**						
Experience of illness scale			**X**	**X**	**X**				
Medical mistrust			**X**						
History of abuse and interpersonal violence			**X**		**X**		**X**		**X**
Social support and conflictual social interaction			**X**						
Brief Pain Inventory			**X**	**X**	**X**	**X**	**X**	**X**	**X**
Brief Symptom Inventory			**X**	**X**	**X**	**X**	**X**	**X**	**X**
Household Food Survey			**X**	**X**	**X**	**X**	**X**	**X**	**X**
EuroQol-5D-5L			**X**						
Crime and legal activities			**X**	**X**	**X**	**X**	**X**	**X**	**X**
Non medical and other services			**X**	**X**	**X**	**X**	**X**	**X**	**X**
Access to care			**X**		**X**		**X**		**X**
Sexual behavior			**X**	**X**	**X**	**X**	**X**	**X**	**X**
Condom use			**X**		**X**		**X**		**X**
Communicating w/ physician about PrEP/HCV Tx self-efficacy			**X**	**X**	**X**				
Relationship with physician			**X**	**X**	**X**				
PrEP adherence HCV-PA1 and 2				**X**	**X**	**X**	**X**	**X**	**X**
Adherence counseling/patient navigation satisfaction survey	**EOI**								

*SCR* screening, *BSL* baseline, *EOI* end of intervention, *M* month

During the second screening visit, a clinician completes a physical exam and informs the potential participants of their lab results. Ineligible participants receive their lab results, proceed as they normally would for routine services, and/or receive health care and treatment based on physician recommendation.

Before study consent and randomization, eligible participants are informed of the pros and cons of being on PrEP to ensure equivalent information for all. Interest in initiating PrEP is not required to participate. Eligible participants who are still interested in participating complete the study informed consent process and sign the IRB-approved consent form.

#### Randomization

##### Randomization arm 1: on-site integrated care with adherence counseling

Participants randomized to the on-site integrated care with adherence counseling arm are offered PrEP and, if indicated, HCV treatment at the site, either the OAT clinic or SSP, where they were recruited or are receiving care/services. Nurses, physicians, and counselors trained in PrEP and HCV treatment meet with participants and provide care directly at OAT and SSP venues. For participants who choose to, the goal will be to initiate PrEP and/or, if applicable, HCV treatment as soon as possible.

Counseling for PrEP initiation and adherence and for HCV treatment is provided by the clinical counseling staff of the on-site integrated care arm. Counseling assesses PrEP and HCV treatment understanding and beliefs; medication adherence, benefits, and adherence strategies; and risk behaviors and risk reduction strategies. Counselors meet with participants to support treatment adherence, discuss barriers, and develop a personalized adherence plan.

As part of the integrated care team, the counselor conducts up to 5 face-to-face sessions over 6 months. These counseling sessions are estimated to be 20 to 35 min in duration and are tailored to each participant’s needs and risk profile. The counselor incorporates Motivational Interviewing (MI) techniques to communicate and build an effective, working relationship with the participant. MI is a patient-centered approach to counseling which recognizes that the participant is ultimately responsible for his/her own behavior change [46–51].

##### Randomization arm 2: off-site referral to specialized care with patient navigation

Participants randomized to the off-site referral to specialized care and patient navigation arm work with a patient navigator to be linked to primary care for PrEP and, if necessary, HCV treatment. We have adapted the Antiretroviral Treatment Access to Services (ARTAS) intervention, an effective linkage to care intervention for persons living with HIV, to facilitate linkage to PrEP and, if necessary, HCV treatment services for PWID [52, 53]. Participants in the off-site care arm are offered continuous PrEP and, if necessary, HCV treatment by their off-site physician.

Patient navigators actively coordinate and link participants to available clinics and community resources by scheduling appointments, arranging transportation, and assisting the participant with completing any clinic registration or health insurance enrolling/re-enrolling paperwork that a clinic or service agent may require. The intervention includes up to 5, 30–45 min face-to-face meetings with the patient navigator and participant. These meetings are tailored to each participant’s needs. Additionally, the patient navigator assists the participant in identifying and utilizing informal and formal sources of support to move along the PrEP and/or HCV care continuum, including accessing and utilizing ongoing substance use treatment and harm reduction services as needed. The patient navigator helps the participant inform off-site physicians of the trial and of the availability of PrEP and HCV medication, should the physician and patient decide to initiate one or both treatments. Brief telephone, email, and text message communication is expected between the patient navigator and care agencies/support services and between the patient navigator and the participant. These non-face-to-face contacts will be logged and tracked but will not be counted as any of the 5 face-to-face intervention meetings.

#### Provision of other medical care (both arms)

In addition to PrEP and, if indicated, HCV care, participants in the on-site integrated care arm receive a referral to ancillary care services consistent with the local standard of care. If required, the off-site physician may provide all necessary care to off-site participants.

#### Medication

Tenofovir disoproxil fumarate/emtricitabine (TDF/FTC, Truvada*®*, Gilead Sciences) and sofosbuvir/velpatasvir (SOF/VEL, Epclusa®, Gilead Sciences) are made available free of charge to participants in both arms. Clinicians are allowed to use other treatment regimens if deemed preferable for the participant.

TDF/FTC is an oral combination to be taken continuously on a once-daily basis [54]. As recommended by CDC and Canadian PrEP guidelines, participants are counseled regarding side effects and monitored every 3 months for adverse events, including signs of renal compromise.

SOF/VEL is an oral combination of sofosbuvir (NS5B inhibitor) and velpatasvir (NS5A inhibitor) [55] taken once daily for 12 weeks. SOF/VEL demonstrated high rates of sustained viral response (SVR; equivalent of cure) in phase III and real-life observational studies for all HCV genotypes [56–60].

### Criteria for discontinuing or modifying allocated interventions (11b)

#### HIV seroconversion

HIV status is monitored every 3 months. Participants who seroconvert during treatment will be immediately discontinued from PrEP and actively referred for proper HIV care.

#### Pregnancy

Participants who become pregnant will be kept in the study, but those taking TDF/FTC will be evaluated for risk by their physician to determine if TDF/FTC should be discontinued. Participants taking SOF/VEL who become pregnant during study participation will be discontinued from this medication.

#### Renal function impairment

Serum creatinine is monitored every 3 months. If a participant’s creatinine clearance decreases to <30 ml/min, serum phosphate decreases to < 1.0 mg/dl, or renal function declines with no other identifiable cause, they will be evaluated by a physician to determine if medication should be discontinued.

#### HCV treatment

HCV treatment will be discontinued in the following situation: a 10-fold increase in ALT level; an increase in ALT <10-fold that is accompanied by any weakness, nausea, vomiting, jaundice, or significantly increased bilirubin, alkaline phosphatase, or international normalized ratio (INR); and a decrease in creatinine clearance below 30 mL/min. Participants who developed decompensated cirrhosis during the trial will be immediately referred to a hepatologist who will evaluate whether treatment should be discontinued.

### Strategies to improve adherence to interventions (11c)

As part of the intervention, participants have up to 5 meetings with the adherence counselor (on-site group) or the patient navigator (off-site group). These meetings are tailored to each participant’s needs but should help them to adhere to the interventions proposed.

Adherence monitoring is based on self-report. In addition, for PrEP, liquid chromatography and mass spectroscopy will be used to detect the presence of tenofovir-diphosphate on dried-blood spots (DBS) [61, 62].

### Relevant concomitant care permitted or prohibited during the trial (11d)

Patients on HCV treatment at screening will have to postpone enrollment until after the end of treatment. Patients currently on PrEP are excluded.

Prior to enrolling in this study, participants may have pre-existing relationships with professionals for the purposes of securing housing, benefits, food, HCV care, HIV prevention, substance use, and mental health treatment. Renewed or continued contact with any such professional or paraprofessional staff may include discussion of HCV prevention and treatment, HIV prevention, and substance use treatment. Regardless of the study group, impeding any such contacts would be both unethical and infeasible. To account for non-study-related professional or paraprofessional contacts, medical records are obtained upon participant consent, and participants are asked about such exposures during follow-up assessments.

### Provisions for post-trial care (30)

Prior to study completion, research staff will connect participants with physicians and care teams in the community as appropriate or within the programs at the site where the study is conducted. Medication will be continued after the study at the patient’s discretion. Prior to study completion, research staff will attempt to connect participants with physicians and care teams in the community as appropriate or within the programs at the site where the study is conducted.

### Outcomes (12)

#### Primary outcome measures

The co-primary trial outcomes are (1) sustained PrEP adherence during the first 6 months and (2) HCV cure among participants living with HCV.

**Table 4 Tab4:** Definition and measure of secondary and tertiary outcomes

Secondary outcomes	Definition	Measure
PrEP initiation/uptake	Receiving a prescription and taking the first dose of the medication	First dose of Rx dispensed to the patient and recorded at pharmacy/dispensing venue + self-report
Long-term sustained PrEP adherence	PrEP use at 6, 12, and 18 months post-randomization	Self-report + detectable level of TDF in DBS 6, 12, and 18 months post-randomization
HCV incidence/re-infection	New HCV infection	At scheduled visit: HCV-Ab positive (never infected) or detectable HCV-RNA (previously infected and cured)
STI or HIV incidence/STI re-infection	New STI or HIV infection in a previously uninfected person/previously infected and cured person	At scheduled visit: Any positive test result for *Neisseria gonorrheae*, *Chlamydia trachomatis*, syphilis, or HIV
Behavioral disinhibition	Changes or increase in sexual or injection risk behaviors	Self-report at each visit
**Tertiary outcomes**	**Definition**	**Measure**
Ongoing PrEP use	Any PrEP use during any period	Any detectable level of TDF in DBS/Self-report of use
HCV SVR within those initiating	12-week sustained viral response post-end of treatment	First dose of medication dispensed to the patient and recorded at pharmacy/dispensing venue + self-report/HCV-RNA negative at 12 weeks post end of treatment

Sustained PrEP adherence will be compared between both treatment arms at 6 months post-randomization. Sustained PrEP adherence will be defined as the self-report of achieving daily PrEP use, which will be confirmed by evidence of detectable levels of tenofovir. In order to achieve protection against HIV infection, TDF/FTC should be taken once daily to achieve protective levels. PrEP use will be self-reported by participants. Blood tenofovir will be detected using DBS collected every month beginning at 8 weeks post-PrEP initiation during the first 6 months post-randomization and subsequently every 3 months during research visits.

HCV cure is defined as initiating HCV treatment within 6 months of being randomized and achieving SVR by 12 months post-randomization. HCV treatment initiation will be measured using self-report and by assessing medical/drug dispensation records. SVR12 is defined as a negative HCV-RNA 12 weeks after end of treatment.

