### Objectives (7)

The primary study objective is to compare the effectiveness of on-site integrated care that includes adherence counseling vs. off-site referral to care with support of a patient navigator in increasing rates of (1) PrEP adherence (0–6 months) and (2) HCV sustained viral response 12 weeks post-treatment completion (SVR12) among PWID recruited in OAT and SSP in Miami, FL, and Montreal, Quebec. The study will examine the relative contributions of living in cities with different healthcare systems (Miami vs. Montreal) and venues (OAT vs. SSP) on primary outcomes.

Secondary objectives are to measure differences between study arms in (1) PrEP initiation, (2) long-term sustained PrEP adherence (6–18 months), (3) HCV infection/reinfection, (4) sexually transmitted infections and reinfection (including HIV), and (5) behavioral disinhibition, i.e., the proportion of participants who increase sexual or injection risk behaviors.

The study will include a qualitative component with the following objectives: (1) to explore individual and structural factors influencing PrEP initiation and adherence; (2) to examine how PWID understand and define PrEP adherence; (3) to describe and understand PWID’s experience regarding on-site and off-site interventions including their perceived effects on PWID’s health; (4) to examine if and understand how PrEP use is related to HIV risk behavior modifications among PWID; (5) to understand facilitators and barriers to implementation and how study staff experience and address these factors during the trial.

Finally, a cost-effectiveness analysis will evaluate (1) healthcare services utilization and cost-effectiveness of the on-site integrated care approach compared to the referral with patient navigator and (2) the healthcare resources required to scale up these intervention approaches in the local environments and site settings.

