We will analyze long-run sustained PrEP adherence and HCV cure resulting from treatment initiated after the first 6 months, similarly, except using a repeated-measures Poisson regression implemented as a generalized estimating equation (GEE) including the periods between 6- and 18-month follow-ups. It is important to note that for all PrEP adherence analyses, any participants who become HIV positive will be counted as PrEP non adherent. For all other secondary outcomes, similar approaches will be used. PrEP initiation will be assessed as a simple binary outcome (initial self-reported use verified by prescription in medical records) and again modeled using repeated measures Poisson regression. We will examine sustained PrEP adherence among those self-reporting taking PrEP to disentangle PrEP non-engagement, inadequate PrEP use, and protective levels of PrEP use. Note that protective levels of PrEP use will be examined only among patients not on HCV medication due to norms for protective PrEP use when taken with HCV medication not having been established. We will examine HCV treatment initiation and rates of SVR among those treated (the primary analysis will include all HCV-positive randomized participants). We will examine potential rates of behavioral disinhibition as measured by changes in self-reported sexual risk (i.e., condom-less vaginal and/or anal sex), needle/works sharing, HCV infection/re-infection rates, and STI (including HIV) infection rates over the entire follow-up period. Additional analyses will examine the timing of initiation of both PrEP and HCV treatment, and whether non-engagement and discontinuation of PrEP are related to levels of (or changes in) risk.

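### Long-term PrEP adherence is defined to include month 6, the co-primary visit at the end of on-site counselling, so a difference seen only at month 6 can show up as a long-term effect

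*Protocol article*

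**What the plan says.** Objectives (7) sets two windows that meet at month 6: "PrEP adherence (0–6 months") for the primary objective and "long-term sustained PrEP adherence (6–18 months") for the second secondary objective.

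Outcomes (12) places the co-primary comparison at month 6: "Sustained PrEP adherence will be compared between both treatment arms at 6 months post-randomization". The measure is "the self-report of achieving daily PrEP use, which will be confirmed by evidence of detectable levels of tenofovir".

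Table 4, in the same section, defines the long-term outcome as "PrEP use at 6, 12, and 18 months post-randomization" and measures it by "Self-report + detectable level of TDF in DBS 6, 12, and 18 months post-randomization".

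Statistical methods (20a) analyses the long-term outcome with a repeated-measures Poisson GEE, "including the periods between 6- and 18-month follow-ups". It mentions neither an arm-by-time term nor a contrast at a single visit.

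The description of the on-site arm says that "the counselor conducts up to 5 face-to-face sessions over 6 months".

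**The concern.** The secondary objective is about persistence: does any advantage of on-site care last once the first 6 months are over? Month 6 cannot show that. It is the visit at which the co-primary is judged, and it comes at the end of the counselling sessions rather than after them. Table 4 nonetheless treats it as one of three outcome measurements, not as a reference point from which persistence is judged.

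If the three visits are summarised by a single arm effect, a month-6 difference that has gone by month 12 still moves the summary away from 1. A positive co-primary result would then make a positive long-term result more likely, even with no difference between the arms at months 12 and 18. A report could call that sustained adherence.

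**Working it through.** **Inputs from the article.** 500 participants allocated 1:1, so 250 per arm; 40% versus 55.5%; alpha .025 for each co-primary; 90% power (Sample size (14)).

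**The plan's own figure.** Two-proportion test, two-sided .025, mean rate 0.4775:
- SE under the null: √(2 × 0.4775 × 0.5225 / 250) = 0.0447.
- SE under the alternative: √((0.4 × 0.6 + 0.555 × 0.445) / 250) = 0.0441.
- Power = Φ((0.155 − 2.241 × 0.0447) / 0.0441) = Φ(1.243) = 89.3%.

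This agrees with the stated 90%, so the rates and sample size can be used as they stand. The article states no figure for the long-term outcome.

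**Scenario (assumed).** 55.5% versus 40% at month 6, and 40% in both arms at every later visit.

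**Pooled risk ratio with one arm effect.**
- Months 6, 12, 18: (0.555 + 0.40 + 0.40) / (3 × 0.40) = 1.355 / 1.20 = 1.13.
- Months 6, 9, 12, 15, 18: (0.555 + 4 × 0.40) / (5 × 0.40) = 2.155 / 2.00 = 1.08.
- Months 12 and 18 only: 1.00.

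**Chance of a significant result favouring on-site care.** The test is log(RR) divided by its robust SE. With within-person correlation c between visits, the person-mean over k visits has variance close to p(1 − p)(1 + (k − 1)c)/k. For k = 3 and c = 0.33:
- Control arm: variance 0.24 × 1.66 / 3 = 0.1328.
- On-site arm: variance 0.1341, mean rate 1.355 / 3 = 0.4517.
- SE = √(0.1341 / (250 × 0.4517²) + 0.1328 / (250 × 0.40²)) = 0.077.
- z = ln(1.129) / 0.077 = 0.1215 / 0.0771 = 1.58.
- Chance of exceeding 1.96: 1 − Φ(1.96 − 1.58) = 35%.

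Simulation (4,000 runs per scenario, correlated binary data from a latent normal variable) gives, at two-sided .05:

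| Within-person correlation (assumed) | Months 6, 12, 18 | Months 6, 9, 12, 15, 18 | Months 12, 18 only |
|---|---|---|---|
| 0.19 | 40% | 21% | 2.2% |
| 0.33 | 35% | 17% | 2.3% |
| 0.49 | 29% | 15% | 2.6% |
| 0.65 | 28% | 14% | 2.4% |

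The hand formula gives 41, 35, 30 and 27% for the first column, in agreement. Fitting Poisson GEEs to 300 simulated trials at a correlation of about 0.5, with one arm effect, gave RR 1.14 and 37% with month 6, and RR 1.01 and 3% without it.

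**Other readings.**
- If sustained means adherent at all of months 6, 12 and 18, the RR is 1.11 to 1.26, and 12 to 16% of trials are significant.
- If adherence declines equally in both arms to 30% and then 20%, the three-visit RR is 1.055 / 0.90 = 1.17, and 32 to 47% are significant.

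The size depends on the reading. The direction does not.

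**The case against.** Several points on the other side stand.

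- **The model wording is open.** Periods between the 6- and 18-month follow-ups can be taken as the intervals after month 6. The GEE would then exclude month 6 and the fault would be a mismatch with Table 4. The two places still need reconciling.
- **The mean structure may be set elsewhere.** The article neither states nor rules out an arm-by-time term, and a statistical analysis plan would normally fix it. Such a term, or separate reporting of each visit, would remove most of the effect computed here. What the article does fix is the outcome definition, and that includes month 6.
- **The scenario is extreme.** Only the counselling sessions are limited to 6 months. Nothing says on-site PrEP care stops then, and no duration is given for the navigator meetings. Complete loss of effect at month 6 is an assumption.
- **The rejections are not false positives for every estimand.** For average adherence over months 6 to 18 with month 6 included, the simulated arms do differ. The figures measure how poorly that average answers a persistence question.
- **Using months 6, 12 and 18 is not in itself an error.** These are the full research visits; months 9 and 15 are short interim ones.

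A reader might go further, in three ways that the article does not support:

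- That one third of the pooled effect is the co-primary result itself. The co-primary concerns daily use over the first 6 months with monthly blood spots, whereas Table 4 speaks of PrEP use, so the two month-6 variables are not shown to be identical.
- That the persistence objective goes unanswered. Months 12 and 18 are measured and named in the definition.
- That the cost-effectiveness model is fed an inflated effect. The article does not say that this pooled ratio enters the model.

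**Conclusion.** The point holds as a weakness in the definition of one secondary outcome. Table 4 mixes the co-primary visit into an outcome meant to describe adherence beyond 6 months, and the methods text leaves open whether the model does the same.

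The consequence is conditional. It needs a single pooled arm effect that includes month 6 and an effect that is gone by the next visit counted. Under those conditions, and for assumed correlations of 0.19 to 0.49, the pooled RR is about 1.13 with roughly 30 to 40% of trials significant for on-site care. With all quarterly visits from month 6 it is about 1.08 with 15 to 21%. Leaving month 6 out restores about 2.5%. If the effect only partly fades, less of the pooled estimate is an artefact of month 6. The co-primary analysis is not affected.

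**What to change.** In Table 4 and in Statistical methods (20a), define long-term sustained PrEP adherence on visits after month 6: months 12 and 18, optionally with months 9 and 15. Leave month 6 to the co-primary outcome. State that the arm contrast will be reported at month 12 and at month 18, alongside any pooled estimate, and make the GEE wording name the visits it uses.

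The cost is a change of wording before the analysis plan is finalised. Dried blood spots (Table 2) and the PrEP adherence questionnaire (Table 3) are already scheduled at months 9, 12, 15 and 18, so no visit, sample or participant is added. The downside is that the pooled long-term estimate may rest on fewer data, particularly if only months 12 and 18 are used, and may be less favourable to on-site care.
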